### Data entry, coding, security and storage

Data will be reviewed quarterly and at mid-point through the study to check for
normality and ranges of data values. The data collected will be entered into a
computer database by a nurse or doctor in the research team and will be checked
by supervising members of the team to ensure high data quality.

The data collected for each participant in the study will be recorded in a case
report form (CrF). Each CrF will be identified by the study number of the
subject concerned. Each participant will be assigned a study number in
sequential order (eg,: FRAXIS 001 through to FRAXIS 050). All information
obtained during the study (with the exception of data given in the informed
consent form) shall be entered into a password-protected computer database in
compliance with the Data Protection Act (2018) and stored on a secured
University approved server.

### Statistical analysis plan

Results will be imported into STATA for data cleaning and statistical analysis.
Since this is a pilot study, analysis will be mainly descriptive. Descriptive
statistics for continuous data will be assessed using means and standard
deviations for normally distributed variables, or medians and interquartile
ranges for skewed continuous variables. Analysis would involve looking at
missing data, drop- out rate which would inform sample size calculation for a
future larger study. Categorical data will be summarised using frequencies and
percentages and comparison between the 2 groups (moderate frailty and no-mild
frailty) done using the chi-squared or Fishers exact test.

Where data are not normally distributed these will be log transformed and
presented as geometric means with their 95% confidence interval. Where data are
not normally distributed even after transformation, these will be presented as
median (IQR) and comparisons between groups done using the Wilcoxon rank-sum
test.

The Primary outcome (change in frailty status) will be compared between the 2
groups using the 2-sample independent t test or a simple linear regression.
Other outcome measures will be analysed in a similar way except if these are
skewed when the Wilcoxon rank-sum test will be used. Similarly, a linear mixed
models approach will be used to study the 2 study time points (baseline and
follow up) in the 2 groups. All tests will be 2 sided and significance will be
set at *P* < .05.

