### Measurements

At recruitment and at follow up, frailty status of participants would be assessed
using the Rockwood/Clinical Frailty score (CFS) and the electronic Frailty index
(eFI) score. The Rockwood/CFS is a frailty assessment spectrum grouped from 1
(very fit) to 9 (terminally ill). The electronic frailty index (eFI) classifies
frailty into 4 groups spanning from fit (eFI < 0.12) to severely frail (eFI
> 0.36). Participants in this study, would be categorised based on their
scores as no-mild frailty (CFS ⩽ 3, eFI ⩽ 0.24) and moderate frailty (CFS 4-6,
eFI 0.24-0.36). The choice of stratifying the study participants into a spectrum
of frailty states from not-frail to mildly frail and moderately frail is based
on the knowledge that progression towards advanced frailty states can be delayed
and/ or reversed if the right intervention is implemented.^31,33,37^

Arterial stiffness will be measured in 2 ways: using Complior^®38^ and
CAVI^®.39^ Assessment of arterial stiffness will be done at room
temperature with the patient supine and after having rested for 10 minutes.
Patients will be asked to refrain from smoking, eating or drinking caffeinated
drinks for 3 hours before measurements and to avoid consuming alcohol for 10
hours before measurements. Participants will be offered reimbursement for travel
expenses.

(a) The Complior^®^ is a non-invasive device which measures Pulse Wave
Velocity and central pressures. The carotid, femoral and radial pulses are
palpated and marked, and measurements are taken between them. The wave forms are
then measured and recorded on the Complior^®^ programme using small
sensors. We will perform at least 2 measurements, and if similar will use the
mean of these. If these differ by more than 0.5 m/s, a third measurement will be
performed. The PWV value should be the median of these measurements.

(b) Cardio-Ankle Vascular Index (CAVI^®^) is another index which
assesses arterial stiffness, this time it uses measurements in all 4 limbs.
CAVI^®^ then equates the stiffness using the pulse wave between the
heart and the ankles. Complior and CAVI measurements will be done by the same
person to ensure consistency. These 2 measurements will be done only once at
baseline and not at follow up since we do not expect any changes within 6
months.

(c) A blood sample will be obtained by a trained research nurse or doctor. The
participant will be asked to give approximately 20 mls of blood (one and a half

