### Sample size

This is a pilot study with no formal sample size calculation done. We aim to
recruit 40 participants who fit the eligibility criteria, but this number will
be adjusted upwards to 50 participants to account for an expected dropout rate
of 20%. We aim to recruit at least 2 participants per week within 5 months. The
selected sample size is considered reasonable for a pilot/feasibility study by
NIHR.^40,41^ Similarly, this is in line with Browne’s rule of thumb
for pilot study sample size calculations which recommends at least 30 subjects
for pilot studies to estimate differences between 2 groups.^42^ It is
further supported by Julious^43^ who suggests that a
minimum of 12 subjects per treatment arm /group is relevant to reduce
imprecision around the estimates of a standard deviation. The chosen sample size
of 50 is a pragmatic approach considering previous studies which used similar
numbers, where 28 frail older adults were compared with 27 robust non-frail
older adults assessing the differences in oxidative stress markers between both
groups.^23^ Participants would be stratified into 2 groups based on
their frailty status as group 1 having no-mild frailty (ie, having a Rockwood
frailty score ⩽3) and group 2 made up of moderate frailty with a Rockwood
frailty score >3 in line with the study’s inclusion criteria. We would aim to
have an equal number of 25 participants in each group.

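### Change in frailty is compared, without baseline adjustment, between groups split on the same baseline frailty score, so regression to the mean biases the primary contrast towards apparent improvement in the frailer group

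*Protocol article*

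**What the plan says.** The Measurements section has frailty scored at both visits with the same two instruments: "At recruitment and at follow up, frailty status of participants would be assessed" "using the Rockwood/Clinical Frailty score (CFS) and the electronic Frailty index". Those scores also define the groups: no-mild frailty is CFS 3 or less (eFI 0.24 or less), and moderate frailty is CFS 4 to 6 (eFI 0.24 to 0.36). The Sample size section repeats the split on the Rockwood score alone, with "group 2 made up of moderate frailty with a Rockwood frailty score >3", and aims for 25 participants per group. The Eligibility criteria cap entry at CFS 6 or eFI 0.36.

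The Statistical analysis plan section then says "The Primary outcome (change in frailty status) will be compared between the 2 groups using the 2-sample independent t test", with a simple linear regression as the alternative. It adds that a linear mixed "models approach will be used to study the 2 study time points (baseline and follow up) in the 2 groups". Tests are two-sided at P < .05. No baseline covariate, repeat baseline measurement or separate grouping instrument is stated.

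**The concern.** An observed baseline score is part stable level and part error or short-term fluctuation. Splitting on the observed score puts people whose score was high by chance into the frailer group, and people whose score was low by chance into the fitter group. At the second visit the chance part is drawn afresh, so the frailer group's mean falls and the fitter group's mean rises. An unadjusted comparison of change counts that drift as a difference between the groups. A group-by-time term in the mixed model would carry the same contrast.

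The primary estimate is therefore biased in a known direction. If nobody truly changes, it favours the frailer group. If frailer participants truly decline faster, the drift offsets that decline and may reverse its sign. The article says the pilot is to provide preliminary data for a larger multi-centre study, and a biased change estimate could be carried into that planning.

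**Working it through.** **The plan's own figure.** Sample size section: 40 / (1 − 0.20) = 50, which reproduces. Then 50 / 2 = 25 recruited per group, and 25 × 0.80 = 20 completers per group.

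**Inputs from the article.** Groups are CFS 3 or less versus 4 to 6; the outcome is change over 6 months; the test is a two-sample t test, two-sided at 0.05, with 20 per group.

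**Assumed, because the article does not give them.** Change is measured on the CFS, with observed mean 3.5 and SD 1.3. Nobody truly changes. The test-retest correlation r of the observed score is varied from 0.65 to 0.95.

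**Closed form** (normal score split at its median).
- Mean baseline in the upper half is 0.3989 / 0.5 = 0.798 SD above the overall mean; the lower half lies the same distance below it.
- Expected change at standardised baseline B is −(1 − r)B. The expected difference in change, frailer minus fitter, is −(1 − r) × 2 × 0.798 = −(1 − r) × 1.596 SD.
- Within-group variance of change, in SD² units, is (1 − r²) + (1 − r)² × (1 − 2/π).
- Standardised difference d is the size of the difference divided by the square root of that variance. The rejection rate comes from the noncentral t with 38 df and noncentrality d × √(20/2).

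At r = 0.90: difference 0.10 × 1.596 = 0.160 SD, or 0.160 × 1.3 = 0.21 CFS points. Variance is 0.190 + 0.010 × 0.363 = 0.1936, so d = 0.160 / 0.440 = 0.363. Noncentrality is 0.363 × 3.162 = 1.147, and rejection is 20%.

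**Simulation on the integer scale.** A constant true score plus fresh error at each visit, rounded and limited to 1 to 9, with entry at 6 or less and 20 per group.

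| Observed r | Closed form, SD | Closed form, CFS points (× 1.3) | d | Closed-form rejection | Simulated, CFS points | Simulated rejection |
|---|---|---|---|---|---|---|
| 0.95 | 0.080 | 0.10 | 0.254 | 12% | about 0.09 | about 11% |
| 0.90 | 0.160 | 0.21 | 0.363 | 20% | about 0.20 | about 19% |
| 0.85 | 0.239 | 0.31 | 0.448 | 28% | about 0.30 | about 28% |
| 0.75 | 0.399 | 0.52 | 0.588 | 44% | about 0.50 | about 44% |
| 0.65 | 0.559 | 0.73 | 0.708 | 59% | about 0.70 | about 58% |

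All differences favour the frailer group. The r in the table is the correlation of the recorded, rounded scores. Rounding adds error of its own: reliabilities of 0.95, 0.90, 0.80 and 0.70 on the underlying continuous score correspond to observed correlations of about 0.90, 0.85, 0.75 and 0.65. At observed correlations of about 0.97 to 0.99 the artefact shrinks to 0.02 to 0.06 points, with rejection near or below 5% to 6%.

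**Masking.** Give everyone with a true score above 3.5 a true worsening of 0.5 points. The mean estimated difference (frailer minus fitter) is then +0.22 at underlying reliability 0.95, but −0.15 at 0.80 and −0.39 at 0.70. The last two have the wrong sign.

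**Check of the remedy.** A second set of simulations, again with no true change, used true-score SD 1.2 or 1.5, underlying reliability 0.60 to 0.95, and 20 or 25 per group. Regressing the follow-up score on group plus continuous baseline score gave a group coefficient between −0.09 and +0.02 and rejection of 4.4% to 6.1%. The t test on change rejected in 17% to 78% of the same trials.

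**The case against.** The strongest reply is that the size is unknown. No reliability or SD is given, and with a very repeatable score the artefact nearly vanishes. That stands: the figures are a range under assumptions, and only the presence and direction of the bias follow from the stated rule.

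A reader might infer that the test will report improvement in the frail and worsening in the fit. The figures do not support that. At observed correlations of 0.95, 0.90, 0.85 and 0.75 about 89%, 81%, 72% and 56% of trials show no significant difference, and these rates apply only if nobody truly changes.

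The article does not say which instrument measures change in frailty status. If groups were formed on one instrument and change taken on the other, the bias would remain only so far as their errors are correlated; nothing in the article says this is intended. Nor does it name a group-by-time term, so the remark on the mixed model is conditional.

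The study is a pilot with no formal sample size calculation, and the items the plan names as feeding the next sample size are missing data and drop-out. That lowers the weight of the P value and the severity of the point. It does not remove bias from the estimate.

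Finally, this is a condensed article and a fuller analysis plan may add covariates. But the outcome, the groups and the test are all stated here, and their combination is the problem, not a missing detail.

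**Conclusion.** The point holds. The stated primary comparison is biased whenever the frailty score has measurement error or short-term fluctuation, and the bias always makes the frailer group look better relative to the fitter group. Under the assumptions above (CFS as the outcome, SD 1.3, 20 completers per group, no true change), the spurious difference runs from about 0.09 points with 11% rejection at an observed correlation of 0.95 to about 0.70 points with 58% rejection at 0.65. The same drift can hide or reverse a true faster decline in the frailer group.

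A reader might go further and call the primary result unusable. The documents do not support that: the size depends on a reliability they do not give, the analysis is largely descriptive, and an adequate covariate is already collected. This is a should-fix.

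**What to change.** In the Statistical analysis plan section:

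1. Do not test unadjusted change between the baseline-frailty groups. Show change by group descriptively, with a note that regression to the mean is expected.
2. Name the instrument that carries the primary outcome. Model its 6-month score in all participants with the continuous baseline score of the same instrument as covariate.
3. Add baseline arterial stiffness or biomarkers to that model, since the abstract's objective names stiffness and inflammaging as predictors. With about 40 completers, add few at a time. Read a coefficient as prediction of the 6-month score at a given observed baseline, because error in the baseline score leaves some true baseline frailty unadjusted.
4. If a group term is kept beside baseline, state that it measures only a step at the cut-point and relies on a linear relation of follow-up to baseline. Apply the same caution to any group-by-time term in the mixed model.

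Cost: no new visits or data. The simple two-group headline test is lost, and the group term is harder to interpret. Step 3 also moves the question from a group contrast to prediction, which the investigators should decide openly and not treat as a wording change. Regrouping on eFI while measuring change on CFS is not a free alternative: recruitment aims for balance on the Rockwood score, so that balance could be lost, and the two instruments' errors would have to be independent, which the article does not state.

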## Dissemination Policy

Patient and Public Involvement (PPI): We secured PPI input from the
Pre-sponsorship review panel (PSRP), incorporating their views in the
formulation of the study protocol, taking them on-board before ethical
clearance and subsequent recruitment of participants. Our PPI rationale is
to ensure the presence of older adults with frailty’s voices throughout the
study from design onwards, so the research stays meaningful and quality
optimised. The PPI advisory group will provide this information throughout
the study. The PPI advisory group will optimise our dissemination strategy
through online and printed material which will be written for non-specialist
audience to assist lay people in understanding the results of the study. We
will also seek to publicise the study through printed press and radio
interviews. Liaising with KSS- geriatric research network and the BGS, will
ensure that the study findings are disseminated. This strategy will help the
planning and recruitment of a larger definitive multi-centre study.Publications: We will publish the findings in high impact journals. All
publications will be published open access or made freely available through
the Universities’ website.Conferences: We will present the study at the highest impact conferences (eg,
British Geriatrics Society annual conference). We will participate in local
events, seminars and conferences. Presentations will be offered to
interested local older adults’ community groups.

We will ensure that the findings of the pilot study are shared with all study
participants who request this information. A study report summarising the main
findings will be sent to the participants through their chosen means (either by post
or by email), using non-technical language which would make it easy to understand.
Participants will be given the opportunity to request further clarification if they
do wish to do so after receiving the study report.
